### 9.4.3 Limitations and Potential Solutions.

The above study approach has limitations. First, the study is essentially non-randomized. Even randomization of hospitals cannot guarantee the balance of confounding factors on the unit of analyses (patients). The cross-over design helps to alleviate this concern as each hospital would be expected to enroll similar populations into each intervention period.

Second, our designed strategies may miss intervention opportunities. Our study design includes pharmacist interventions during business hours on Monday through Friday and does not include weekend interventions. This inclusion criterion will impact Strategy 1 more than Strategy 2, as no alternative approach is available for Strategy 1. To overcome this limitation for Strategy 2, we will allow the intervention to occur within 72 hours of prescription **± 24 hours**, if necessary. This window for intervention will be adequate to intervene on all antibiotic prescriptions. We believe that this approach is appropriate, as we suspect this approach is likely to mirror how most hospitals will eventually implement each of these interventions; thus, it is more likely to lead to true conclusions regarding the feasibility and outcomes of each of these interventions.

Third, the short study period and limited study sites will hinder our ability to demonstrate definitive changes in our secondary analyses, including changes in antimicrobial utilization. The primary goal of this study, however, is to assess feasibility.

Next, the effectiveness of any stewardship program is likely to vary depending on the experience and expertise of the pharmacist performing the PAR and local hospital culture. In fact, we will specifically measure pharmacist variables (e.g., years of experience, experience with stewardship, and training in infectious diseases) to identify barriers to successful implementation of PAR. We will, however, perform pre-intervention standardized training for all pharmacists by a highly experienced and seasoned pharmacist educator in order to make sure all participating pharmacists have appropriate competency.

Given that the strategies are applied at the hospital level, there is the potential for selective entry, i.e., patients and others may be aware of the stewardship strategy prior to enrolling into the study.

Finally, as the primary control group is historical, subsequent comparisons may be biased by temporal effects. The crossover nature of the trial design helps to alleviate this bias inherent to comparing the AS interventions in pooled analyses.

## 533 **10 STUDY IMPLICATIONS**

534 Results from this study will provide valuable information for planning a large, multicenter study  
535 investigating one or both of the proposed interventions in community hospitals. For example,  
536 subsequent research could be limited to one intervention, depending on the feasibility  
537 determined in this pilot study. In addition, important parameters will be available to inform  
538 power calculations for future cluster-randomized trials.

539        **11 PARTICIPANT CONFIDENTIALITY**

540        Appropriate waivers of consent and HIPAA authorization will be obtained at all sites.

541        **12 INFORMED CONSENT PROCESS**

542        Appropriate waivers of consent and HIPAA authorization will be obtained from all local IRBs  
543        overseeing hospitals.

544        **13 SOURCE DOCUMENTS AND ACCESS TO SOURCE**  
545        **DATA/DOCUMENTS**

546        No source documents will be used by this protocol.

547

548        **14 QUALITY CONTROL AND QUALITY ASSURANCE**

549        The PI will ensure that all study personnel are appropriately trained and applicable  
550        documentations are maintained.

551        The DCRI will implement a Quality Plan to, at a minimum, ensure that activities proposed by the  
552        PI to ensure protocol training, data quality and data security are being undertaken.

553

## **15 ETHICS/PROTECTION OF HUMAN PARTICIPANTS**

### **15.1 Institutional Review Board**

The investigator will ensure that the protocol is reviewed and approved by the appropriate IRB prior to the start of any study activities. The IRB will be appropriately constituted and will perform its functions in accordance with US regulations, ICH Good Clinical Practice guidelines, and local requirements as applicable.

### **15.2 Informed Consent**

This study does not involve the enrollment of participants; appropriate waivers of consent and HIPAA authorization will be obtained from all local IRBs overseeing hospitals.

### **15.3 Data Confidentiality**

The study protocol, documentation, data, and all other information generated by this study will be maintained in a secure manner and will be kept confidential as required by law. In order to meet federal or state regulations, this information may be reviewed by the FDA, IRBs, the sponsor and its representatives, or the NIH.

Data access will be limited to study personnel, and the data will be stored on servers with limited physical access (e.g., locked rooms) and limited electronic access (e.g., password-controlled access to data, computers, and, if applicable, networks). No information concerning the study or the data will be released to any third party without prior written approval of the ARLG.

### **15.4 Study Discontinuation**

This study may be terminated at any time by the PI in consultation with the ARLG.

## 16 DATA HANDLING AND RECORD KEEPING

### 16.1 Data Management Responsibilities

The hospitals will enter data into the ARLG DICON1 database via Research Electronic Data Capture (REDCap; see Data Capture Methods below). Other data will come from the ARLG DICON1 EHR database. DICON Network personnel will reconcile the data, strip out the MRN identifiers, and provide DCRI with an ARLG DICON1 limited database with the DICON ID as the subject identifier. These limited datasets will be sent to DCRI as the data coordinating center. DCRI will send the data to the Harvard Statistical Center for analysis.

### 16.2 Data Capture Methods

REDCap is a toolset and workflow methodology for electronic collection and management of research and clinical trial data. Both REDCap and REDCap Survey systems provide secure, web-based applications that are flexible enough to be used for a variety of types of research, provide an intuitive interface for users to enter data and have real time validation rules (with automated data type and range checks) at the time of entry. These systems offer easy data manipulation with audit trails and reporting for reporting, monitoring and querying patient records, and an automated export mechanism to common statistical packages (SPSS, SAS, Stata, R/S-Plus).

The REDCap program will serve as the portal for data entry at remote study hospital locations. Data entered into this database will be password protected and only accessible by study personnel. All access to this secure separate database will be monitored and logged.

This REDCap database will be created and managed by the DCRI and hosted by DOCR at Duke. MRN will be stripped from REDCap data sent to DCRI.

EHR data from the hospitals are sent to Duke DASON from each of the study hospitals through routine DASON activities. These data files are sent via secure File Transfer Protocol (sFTP) to servers and are available on shared drives kept behind DUHS firewalls. By standard DASON procedure, these data are typically stripped of PHI except dates prior to transmission to DUHS. Individual patients are instead identified by a "DICON ID". For the purposes of this study, however, we will eliminate the step that removes PHI so that MRN is provided in these files. This specific data variable is required to connect the data received from the pharmacist intervention database to the EHR database. The MRN will be stripped out of the datasets sent to DCRI.

**Specific Data Management.** Given the number of hospitals involved in the study and the various types and sources of data to be used, consideration must be given to each type and location of data required for the study.

1. Pharmacist intervention forms - These REDCap forms will be created and managed by DCRI and hosted by DOCR at Duke. The pharmacist at each site will complete these forms for each intervention. These data will include PHI such as MRN. Data from these forms represents the only subject level data specifically generated for this study. MRN data will not be included in the transfers to DCRI.
2. Pharmacist time forms - These REDCap forms will be completed by the pharmacist at each hospital and will provide information concerning the time spent on the interventions.
3. Hospital level forms - These REDCap forms will be completed by DASON personnel. These data will include information regarding the approval and implementation of the stewardship strategies at each hospital
4. Questionnaires - These REDCap questionnaires will be completed by the pharmacists and prescribers at each hospital after each strategy is completed (at the end of the six month period). Pharmacists and prescribers will be sent a link to the questionnaires in order to complete. These will not require a REDCap account.
5. Pharmacy data - Antimicrobial utilization data are sent to Duke DASON from each of the study hospitals through routine DASON activities. These data will include PHI such as MRN and dates. These data are created through routine hospital pharmacy activities. These data files will include PHI such as MRN and dates. These data will be transmitted to DUHS via the same sFTP established for routine transmission of data described above. MRN data will not be included in the transfers to DCRI.
6. Bed Flow and Admission-Discharge-Transfer (ADT) data – We will receive bed flow (patient movement within the hospital) and ADT files from study hospitals on a monthly basis through standard DASON activities. These data files will include PHI such as MRN and dates. These data will be transmitted to DUHS via the same sFTP established for routine transmission of data described above. MRN data will not be included in the transfers to DCRI.
7. Demographics data - We will receive data from study hospitals on a monthly basis through standard DASON activities. These data files will include PHI such as MRN and dates. These data will be transmitted to DUHS via the same sFTP established for routine transmission of data described above. MRN data will not be included in the transfers to DCRI.
8. Billing/ICD-9 data - We will receive data from study hospitals on a monthly basis through standard DASON activities. These data files will include PHI such as MRN and dates. These data will be transmitted to DUHS via the same sFTP established for routine transmission of data described above. MRN data will not be included in the transfers to DCRI.
9. Microbiology data - We will receive data from study hospitals on a monthly basis through standard DASON activities. These data files will include PHI such as MRN and dates. These data will be transmitted to DUHS via the same sFTP established

649 for routine transmission of data described above. MRN data will not be included in  
650 the transfers to DCRI.

651 **16.3 Study Data Retention**

652

653 Research records and data must be kept for a minimum of 6 years after final reporting or  
654 publication.

655 **16.4 Protocol Deviations**

656

657 Not applicable.

## 658        **17 PUBLICATION POLICY**

659        Following completion of the study, the investigator may publish the results of this research in a  
660        scientific journal under the oversight of the Publication Committee of the ARLG.

661

## 1. Introduction

The purpose of this document is to describe the analyses proposed for the analysis of DICON. The plan includes the key analyses that will form the core of any presentation or publication used to disseminate the primary conclusions of the study.

We intend to do multiple reports for DICON. The potential reports include:

- Feasibility, Provider perceptions, REDCap Summary tables
- Secondary objectives, focusing on Days of Therapy (DOT) and patient specific outcomes including total hospital days, Death and Intensive Care unit admission
- Exploratory objectives.

## 2. Core Manuscript writing team

To be determined.

## 3. Study overview

### 3.1 Study Design

DICON is a three stage, multicenter cluster randomized historically controlled crossover trial to determine the feasibility and outcomes from two antimicrobial Stewardship interventions in community hospitals.

The three stages of the study are:

- Stage 1: One year of retrospective data from hospitals
- Stage 2: Two hospitals implement stewardship strategy one for six months, while the other two hospitals implement stewardship strategy two for six months. This is followed by a one month washout period.
- Stage 3: Strategy 1 hospitals implement strategy 2 and strategy 2 hospitals implement strategy 1.

The two study strategies are:

Stewardship Strategy 1 – Antimicrobial restriction and Pre-authorization. Following approval of the protocol at study hospitals, all prescriptions for targeted antibiotics will require phone approval by the trained PharmD. Prescribers will be instructed to discuss the patient details and the rationale for the desired antimicrobial with the PharmD. Specifically, prescribers must contact the pharmacist via pager or phone call to discuss the rationale for using the targeted antibiotic. The pharmacist will discuss the rationale and the specific clinical scenario with the prescriber and will decide if the targeted antibiotic is approved or denied. If the pharmacist denies the use of the targeted antibiotic, the pharmacist will provide recommendations for alternative antibiotics for the specific clinical scenario. The pharmacist will then document this interaction in the REDCap database, documenting

which targeted antibiotic was requested, the prescriber's rationale for requesting the targeted antibiotic, the patient's symptoms and pertinent clinical data at the time of the request, whether the request met the criteria for use of the targeted antibiotic (or not), and the pharmacist's recommendation. Prescriptions for targeted antibiotics will be eligible for intervention if written between 7am and 6pm Monday through Friday. Off-hours prescriptions will be reviewed for approval for continuation the following morning.

Stewardship Strategy 2 – Post-antibiotic Review and Feedback. Following approval of the protocol at study hospitals, all prescriptions for targeted antibiotics will be reviewed by the study pharmacist approximately 72 hours after initially written. The clinical pharmacists will review a list of patients receiving the targeted antibiotics on a daily basis to identify patients who have received one or more targeted antibiotics for 72 hours ( $\pm$  24 hours). The pharmacist will review and document the patient's current symptoms, pertinent clinical data, and the indication for the targeted antibiotic documented in the chart. Based on this review, the pharmacist will decide if the targeted antibiotic is necessary and/or if it needs to be modified. If a change is recommended, the pharmacist will then contact the prescriber (i.e., by pager, by phone call, or during clinical rounds) to discuss the pharmacist's recommendations. The interaction will be documented in the REDCap database, including whether or not the prescriber is going to follow the pharmacist's advice. If the pharmacist concludes that the antibiotic is appropriate, then he or she will document that the antibiotic is appropriate but will not be required to contact the prescriber.

Follow up: Strategy 1 and Strategy 2 -- For both strategies, the pharmacist will review the patient's chart approximately five days after interacting with the prescriber to document whether the pharmacist's recommendation was followed. The pharmacist will specifically document if the recommendation was followed, the recommended duration of antibiotic, whether the dose of the antibiotic was appropriate, and the ultimate infection diagnosis. If the patient has already been discharged, the pharmacist will review the patient record to gather this information.

### 3.2 Randomization

The study was randomized by pairs of hospitals based on bed size. The four hospitals participating in the study were paired based on bed size as listed in the AHA Guide, 2013 edition.

The pairs were Pair 1: Maria Parham Medical Center (102 beds) and Wilson Medical Center (220 beds) and Pair 2: Wayne Memorial Hospital (274 beds) and Southeastern Regional Medical Center (373 beds).

The 2 Stewardship strategies were ordered as Option 0: Formulary restriction and Pre-Authorization for the first six months followed by Post-antibiotic prescription review (PAR) for the second six month period or Option 1: PAR for the first six months followed by formulary restriction for the 2nd six months. A binomial outcome was randomly generated (Bernoulli 0.5) in SAS 9.1 for the ordering of the strategies for the smaller hospital in each pair, with the 2nd hospital receiving the strategies in the opposite order. A set seed was used for reproducible results.

The results of the randomization were:

|              |                                            |                                            |
|--------------|--------------------------------------------|--------------------------------------------|
| Maria Parham | 1. Formulary Restriction/Pre-Authorization | 2. PAR                                     |
| Wilson       | 1. PAR                                     | 2. Formulary Restriction/Pre-Authorization |
| Wayne        | 1. PAR                                     | 2. Formulary Restriction/Pre-Authorization |

1. Formulary Restriction/Pre-Authorization 2. PAR

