## 3.5 General statistical considerations

- Tables will be presented by Hospital and intervention; each of the 4 sites will be evaluated separately.
  - Stratified pooled analyses may also be conducted
- Dates will not be shown, but converted to days from intervention (intervention) or first hospital contact (feasibility).
- Each Table/Figure/Listing will be annotated with the name and location of the program used to create it, including its location directory.
- All programs that create permanent study-specific derived datasets or that contribute to analyses of the primary or secondary objectives will be validated according to CBAR SOPs
- Categorical variables will be summarized with n and proportion
- Continuous variables will be summarized with mean, sd, median, Q1, Q3, min and max.
- For secondary analyses, there are 3 contrasts of interest
  - PAR vs. historical control
  - Formulary Restriction/Preauthorization (Res/PreA) vs historical control
  - PAR vs Res/PreA
- For each contrast, the difference in outcomes will be estimated using 95% confidence intervals
  - Difference in proportion with 95% CIs for binary outcomes
  - Difference in means with 95% CIs for continuous outcomes

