### 3.5.1 Cluster Randomization and Analysis

This antimicrobial stewardship study was implemented at four hospitals, where each hospital is considered a single cluster. Cluster randomized trials can be analyzed at the cluster level or the patient level. Ideally, analyses are conducted on the cluster level as this is the unit of randomization. However, we will analyze this study using the patient as the unit of analyses as there are only four clusters.

Since randomization occurs at the cluster level but analyses must be conducted at the patient level, the benefits of randomization (i.e., expectation of balance of confounding factors) cannot be assumed. The small sample size of 4 clusters may also negate the benefits of randomization. The crossover nature of the design will help to balance confounding factors as each hospital can serve as its own control. However, as the crossover occurs at the cluster level, and the patients are neither randomized nor crossed-over, it does not have the same advantages as a standard crossover trial and it does not eliminate within-patient variation; the analyses cannot be “paired”.

Since the effect of the intervention is not only a function of the intervention itself but also of the pharmacist, there is potential for considerable site variation in response. Thus each of the four sites will be evaluated separately. Stratified pooled analyses may also be conducted.

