  - Admissions where the antibiotic was not received will have a DOT of 0.
- Modeling (1 model for each of the antibiotics of interest)
  - The purpose of the model is to look at the effect of the intervention on DOT for each antibiotic of interest
  - Dependent variable = DOT for each antibiotic
  - Adjusting for hospital, study period, AS strategy, calendar time, demographic variables
  - The interactions of study period \* strategy, hospital \* study period, hospital \* strategy, will be explored.

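### Strategy order was randomised within two bed-size pairs, but no pooled analysis uses the pairs; period shifts that differ between them can leak, modestly, into PAR vs restriction

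*Combined protocol and SAP*

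**What the plan says.** SAP section 3.2: "The study was randomized by pairs of hospitals based on bed size". The pairs are 102 and 220 beds, and 274 and 373 beds. Order was drawn for the smaller hospital of each pair, "with the 2nd hospital receiving the strategies in the opposite order". As realised, the 102- and 373-bed hospitals have restriction first, and the 220- and 274-bed hospitals have PAR first. (The label of the 373-bed row is lost in the text, but its order follows from the opposite-order rule.)

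On the unit of analysis, SAP section 3.5.1 says: "However, we will analyze this study using the patient as the unit of analyses as there are only four clusters". Contrasts are shown hospital by hospital. On pooling, SAP sections 3.5 and 3.5.1 say only: "Stratified pooled analyses may also be conducted". No stratum or weights are given.

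Two models combine hospitals:
- **SAP section 10**, one DOT model per antibiotic: "Adjusting for hospital, study period, AS strategy, calendar time, demographic variables". Interactions, including hospital by study period, are to be explored.
- **Protocol section 9.4.1.3**: fixed treatment and period, random site and random period-by-site, plus demographics.

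Neither contains pair or pair-by-period. SAP section 3.5.2 relies on the crossover, in pooled analyses, to reduce temporal bias when the two interventions are compared. It also warns that temporal effects may differ across the two periods and that drug shortages occurred during the study.

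**The concern.** Hospital terms absorb the level of each pair but not its change from Period 1 to Period 2. A common period or calendar-time term removes only the shift that all hospitals share. If the smaller and larger pairs shift by different amounts, for example through season or drug supply, the remainder cancels only when the larger pair has the same share of the weight in both order groups. With the patient as the unit, the shares follow patient volume and need not match. Part of the difference in shift would then be read as a difference between PAR and restriction. The randomisation provides a contrast free of this, and the plan does not call for it.

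**Working it through.** **The plan's own figure.** Protocol section 9.1 gives 97% within-hospital power for 0.50 vs 0.55 with 3000 patients per period and alpha 0.05 (two-sided assumed). z = [0.05 − 1.96·√(2·0.525·0.475/3000)] / √[(0.25 + 0.2475)/3000] = (0.05 − 0.02527)/0.01288 = 1.92, so power is 97.3%. It reproduces. It serves here only for scale; the documents give no figure for the pooled contrast.

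**Inputs.** Bed sizes and realised order come from SAP section 3.2. Hospital volumes are not given, so three assumptions are run. The calculation covers Periods 1 and 2 only, that is, eight hospital-period cells.

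**Leak under fixed hospital, common period and strategy.** Let d1 and d2 be the period shifts in the smaller and larger pairs, and τ the PAR minus restriction effect. A restriction-first hospital changes by its shift plus τ; a PAR-first hospital changes by its shift minus τ. The estimate of τ is half the difference between the volume-weighted mean changes of the two order groups, so

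bias = ½ × [larger pair's weight share in restriction-first − its share in PAR-first] × (d2 − d1).

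| Volume assumption | Share, restriction-first | Share, PAR-first | Factor |
|---|---|---|---|
| Equal | 0.500 | 0.500 | 0 |
| √beds | 19.31/29.41 = 0.657 | 16.55/31.39 = 0.527 | 0.065 |
| Beds | 373/475 = 0.785 | 274/494 = 0.555 | 0.115 |

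Weighted least squares on the eight cells gives the same factors. With pair-by-period in place of the common period term, the factor is 0 in every row.

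**Scale.** Assume bed-proportional volume, 14,400 patients per strategy (4 × 3600) and SD 0.5. The patient-level SE of the pooled contrast is then 0.0059. The gaps below are illustrations; the documents give no estimate of d2 − d1.

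| Gap d2 − d1 | Bias | Bias/SE | Type I error (nominal 5%) |
|---|---|---|---|
| 2 points | 0.23 points | 0.39 | 6.8% |
| 5 points | 0.58 points | 0.98 | 16.5% |
| 10 points | 1.15 points | 1.96 | 50% |

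**With the protocol's random period-by-site term.** At assumed SDs of 0.005, 0.01, 0.02 and 0.05 for that term, the 0.115 factor falls to 0.095, 0.062, 0.026 and 0.005. If the SD is instead estimated by REML in the three scenarios above (hospital kept fixed), the biases become 0.20, 0.10 and 0.05 points. The larger the gap, the more the model equalises hospital weights.

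**Hospital-by-period as fixed effects.** Strategy plus all eight hospital-period cells makes 9 columns of rank 8, so strategy is aliased. This exploration cannot stand in for pair-by-period, which leaves strategy estimable.

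**Shift in one hospital only.** Absolute leak per unit shift, bed-proportional volumes:

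| Hospital | Common period | Pair-by-period |
|---|---|---|
| 102 beds | 0.107 | 0.153 |
| 220 beds | 0.223 | 0.153 |
| 274 beds | 0.277 | 0.347 |
| 373 beds | 0.393 | 0.347 |
| Sum of squares | 0.2922 | 0.2876 |

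**Precision.** In bed units the variance is proportional to 0.5·(1/475 + 1/494) = 0.002065 without pairs, and to 0.5/(102·220/322 + 274·373/647) = 0.002196 with pairs. The SE ratio is √(0.002196/0.002065) = 1.031 (0.0059 to 0.0061). On the eight cells, residual degrees of freedom go from 2 to 1, and the t critical value from 4.30 to 12.71.

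**The case against.** The strongest reply is that no patient-weighted pooled contrast is written anywhere. Contrasts are per hospital, pooling is optional, and an unnamed stratum could turn out to be the pair. This stands for the stratified pooled analyses. It does not cover the SAP DOT model, which combines hospitals and, fitted by ordinary methods to patients, weights them by volume.

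Second, the protocol's random period-by-site term nearly removes the leak when the gap is large. That is correct, and any statement of size must say so. But the SAP DOT model does not make the term random, and its variance would be estimated from very few cells.

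Third, volumes are unknown. The only volume figure, at least 600 admissions a month, is a floor that does not distinguish hospitals, and at equal volumes the leak is zero. This stands.

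Fourth, hospitals in a pair may not share a shift: the smaller pair spans 102 to 220 beds, and 220 is closer to 274. This stands too. For a shift in a single hospital the change helps two hospitals and hurts two, with the sum of squared leaks about level.

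A reader might also infer that the pairing was meant to guard against differential period shifts, or that pair stratification makes the pooled estimate free of period bias. The documents support neither. Protocol section 4 credits the reversed order with seasonal protection and describes pairing only as by bed size, and shifts specific to one hospital remain after the change.

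**Conclusion.** The gap is real but small. Order was randomised within pairs, no planned pooled analysis uses the pairs, and the stratum of the pooled analysis is undefined. Under a patient-level fit with fixed hospital and common period terms, between 0 and about 11.5% of the between-pair difference in period shift enters PAR vs restriction, across volume assumptions from equal to bed-proportional. With the protocol's random term the share is much smaller.

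It would be tempting to conclude that the pooled comparison is biased by a known amount. The documents do not support that: they give neither the volumes nor any evidence that the pairs shift differently. The leak also averages to zero over the randomisation, though not for the order realised.

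The single-hospital PAR vs restriction contrasts are more exposed, since each carries the whole of that hospital's period shift. This makes a well-defined pooled estimate more useful. Only secondary analyses are affected; the primary feasibility analysis is descriptive. This is an inexpensive improvement, not a serious defect.

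**What to change.** Amend SAP sections 3.5 and 10 as follows:
- Name the two randomised pairs as the strata of the pooled PAR vs restriction/preauthorization analysis, and state the weights.
- In the Period 1/Period 2 model, replace the common study-period term with pair-by-period. Equivalently, take half the difference between the restriction-first and PAR-first changes within each pair and combine the two.
- Report both pair estimates beside the pooled one.
- State that shifts specific to one hospital are not removed.

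No separate test of pair is needed. The change is to SAP wording only, with no new data. The patient-level SE rises by up to about 3%. If the interval is based on hospital-period cells, the single residual degree of freedom makes it very wide, so the main use is for the pooled point estimate.
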